## Abstract

This trial aims to investigate the effects of the ActTeens physical activity program, on adolescents’ physical activity level, health-related fitness, cardiometabolic and mental health. The trial will aim to recruit ~140 adolescents (aged 13–14 years). Participants will be randomized into either intervention or control groups. The intervention will be guided by social cognitive theory and self-determination theory and implemented over one school term (24-weeks). The *ActTeens Program* will include: (1) structured physical activity sessions delivered within physical education, including movement-based games and dynamic stretching warm-ups; resistance training skill development; high-intensity training workouts; and cool-downs; (2) self-monitoring plus goal setting for physical activity by pedometer-smart wearable; and (3) healthy lifestyle guidance (social support) by WhatsApp® messages about healthy eating and regular physical activity for the intervention and parents groups. Study outcomes will be assessed at baseline, 24-weeks from baseline, and 12-months from baseline. Physical activity (accelerometer) is the primary outcome. Secondary outcomes include muscular and cardiorespiratory fitness, cardiometabolic profile, and mental health. A process evaluation will be conducted (i.e., recruitment, retention, attendance, and program satisfaction). This project will have the potential to address many questions and debates regarding the implementation of physical activity interventions in low-and- middle-income countries.

**Trial registration:** ClinicalTrials.gov NCT05070377. Registered on 7 October 2021.

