### Blinding and randomisation

Randomization will occur among schools that have been recruited and have completed baseline assessments. The schools will be matched based on the following characteristics: school area-level socioeconomic status (i.e., using Socio-Economic Class ABEP) [44]. Schools will be randomised to either a control or an intervention condition by an independent researcher using a computer-based random number generator. We will aim to recruit two classes per school (ie, one class of 8 grade and another of 9 grade) (Fig 1). Schools selected to the intervention condition will participate in the program during the study period, whereas schools allocated to the control condition will continue usual school practice.

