Provision of teacher handbook, fitness equipment, and session resources, provided by the research team	Once	Schools will be provided facilitator handbooks, sets of circuit cards and fitness equipment packs.
Interactive seminar	1×1 hour seminar	Students will participate in an interactive seminar by a member of the research team. The interactive seminar will provide important information about the programme components and behavioural messages (including current recommendations for youth physical activity, healthy eating, screen-time). It will also address relevant information on physical, metabolic and mental health.
Structured physical activity program	2/week	The session will include bodyweight and elastic tubing resistance training, aerobic-based and strength-based activities, and high-intensity fitness challenges that will be run at school during physical education lessons for 16 weeks (2 times per week). Each exercise session will last approximately 20 min. Students will be able to select from a variety of pre-designed cards incorporating both aerobic-based and resistance-based exercises. Behavioural messages (i.e., be physically active, limit screen time, foods, and sugar-sweetened beverages) will be reinforced at the end of sessions (e.g., cooldown).
Pedometer plus goals setting	16-week	The pedometer plus goals setting will be used as a strategy to promote participation in PA of adolescents (out of school). Participants will wear Yamax SW700 pedometers for physical activity self-monitoring and will receive a new goal-setting (based on the number of steps measured in the baseline week) to achieve weekly. The goals setting will be progressive and changed every two weeks, and this strategy has as its objective propose a realistic goal setting aim to achieve at least 10000–11700 steps/day.
e-health	Twice per week	Adolescents of the intervention group will receive messages about healthy behavior (i.e, active lifestyle and healthy eating) by WhatsApp®.
Parental involvement	Once per week	Parents of intervention group students will receive weekly messages about the benefits of physical activity and healthy eating by WhatsApp® to support their adolescent’s healthy behavior change at home.

Adapted by Resistance Training for Teens program [34]–RT: Resistance training; IG: intervention group.

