### Process evaluation

Feasibility will be assessed based on the following: 1) consent rate (how many participants offered the program agreed to be involved); 2) retention rate (retention rate at 24-weeks follow-p); 3) attendance (student participation in the structured PA), 4) students´ satisfaction with the program (“I enjoyed participating in the sessions on 5-point Likert scale: 5 = strongly agree to 1 = strongly disagree) (S4 File), 5) engagement (student engagement with the pedometer self-monitoring and adherence to goals setting) and 6) practical session fidelity (three observations per teacher) using the SAAFE observation checklist [48] (S4 File).

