### Statistical analyses

#### Analysis plan

Linear mixed models will be used to analyze the primary and secondary outcomes using IBM SPSS Statistics for Windows (version 20.0; 2010 SPSS Inc, IBM Company, Armonk, NY 2010 SPSS Inc., IBM Company, Armonk, NY), with significance set at p< 0.05. All analyses will subscribe to the intention-to-treat principle, whereby all participants will be included in the analysis in the group to which they were randomized. The models will be used to assess the effect of treatment, time and the group-by-time interaction, using random effects to account for the clustered nature of the data. Time and treatment will be included as fixed factors, with school class will be included as a random effect. According previous studies, school-level clustering is negligible after accounting for clustering at the class level [72]. However, if requerid, we will test this assumption and additionally adjust our analyses for school-level clustering. Mixed models are consistent with the intention-to-treat principle, assuming that data are missing at random. The analyses of the primary endpoint (ie, 24 weeks endpoint) will be performed using a repeated measures analysis of covariance applied using mixed linear models. Change from baseline to the postintervention of primary and secondary outcomes will be applied as the dependent variable, treatment (intervention or control), time (baseline and 24 weeks), and the group-by-time interaction will be included as independent variables. To examine the maintenance of the effect of the physical activity program on primary and secondary outcomes, comparable repeated measures approach will be used between group (intervention or control), time (baseline, 24 weeks and 48 weeks), and group-by-time interaction. Effect sizes between groups will be calculated using Cohen’s *d* (the adjusted difference between the control and intervention groups over time divided by the pooled standard deviation of change) and interpreted as follows: *d* = 0.2 (small), *d* = 0.5 (medium), and *d* = 0.8 (large). Potential moderators will be explored using linear mixed models with interaction terms for the following: sex (male, female), socioeconomic status (low, medium, high), and initial BMI status (healthy weight vs overweight/obese). Subgroup analyses will be only conducted if significant interaction effects P≤0.10. Sensitivity analyses will be performed (eg, multiple imputation and complete-case analysis). If the intervention effect estimate differs differs significantly from that obtained when these values are included, both results will be reported in the paper. For completeness in assessing the effect of missingness, we will also conduct one per-protocol analyses (ie, at the student levels). Therefore, our student-level per-protocol analysis, we will include only those students who participated at least 80% of sessions offered across the intervention period (up until our primary end point). Hypothesized mediators (Fig 2) of physical activity behavior change will be examined using structural equation modelling to assess the underlying causal pathways of the intervention.

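### The 80%-attendance per-protocol analysis compares self-selected intervention students with unselected controls and cannot serve its stated purpose as a check on missing data

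*Protocol article*

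**What the plan says.** The Analysis plan makes a linear mixed model the main analysis. It states that all analyses follow intention-to-treat, so that "all participants will be included in the analysis in the group to which they were randomized". The model is said to rest on data being missing at random. Multiple imputation and complete-case analysis are named as sensitivity analyses. The section then adds: "For completeness in assessing the effect of missingness, we will also conduct one per-protocol analyses". The set is defined at student level: "we will include only those students who participated at least 80% of sessions offered across the intervention period", counted up to the primary end point.

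Other sections fix who can have an attendance record. Under Blinding and randomisation, the programme goes to one arm only, and "schools allocated to the control condition will continue usual school practice". Process evaluation defines "attendance (student participation in the structured PA" sessions and names no counterpart for control students.

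The number of sessions offered is not settled. Table 1, under Intervention, has them "run at school during physical education lessons for 16 weeks (2 times per week". The Abstract has the intervention "implemented over one school term (24-weeks".

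**The concern.** There are two problems, both in wording that the article itself fixes.

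First, the inclusion rule can select in one arm only. Students who attend at least 80% of sessions may well differ from the rest in motivation, health and habitual activity. Setting them against controls who went through no such filter loses the protection of randomisation. If attenders are the more active students, the result will sit above the intention-to-treat estimate even when the programme does nothing.

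Second, the purpose given does not match the analysis. Dropping students for low attendance changes the question from the effect of being allocated to the programme to something about adherence. It does not vary any assumption about unobserved outcomes. Agreement with the main result could be taken as reassurance about missing data, and disagreement as a sign of a missing-data problem. Neither inference would be sound.

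**Working it through.** No sample size, power or alpha figure in the article depends on this rule, so there is no stated figure to reproduce. The check is one of logic, followed by an illustration of size.

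**Who can meet the rule.** Control students are offered 0 structured sessions, so the 80% criterion is undefined for them. The analysis can run only if controls enter without selection or under a rule that the article does not give.

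**Whether it addresses missingness.** Attendance at sessions and possession of valid accelerometer data are separate facts about a student. A student with complete accelerometry can fall below 80% and be excluded. A student with no valid follow-up accelerometry can exceed 80% and still contribute no outcome. The rule therefore neither isolates nor varies the missing data.

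**Base of the 80%.** At two sessions a week:
- 16 weeks: 2 × 16 = 32 sessions; 0.8 × 32 = 25.6, so at least 26.
- 24 weeks: 2 × 24 = 48 sessions; 0.8 × 48 = 38.4, so at least 39.

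**Size of selection under no programme effect.**

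Inputs from Sample size calculation: SD of MVPA 17.8 min/day, baseline to follow-up correlation 0.59, target difference 5 min/day.

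Assumptions, not in the documents: the share p of intervention students reaching 80% (50% to 90%), and the correlation ρ between attendance propensity and MVPA (0.1 to 0.3). In the baseline-adjusted calculation, ρ is the correlation that remains after adjustment.

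Residual SD after baseline adjustment = 17.8 × √(1 − 0.59²) = 14.4 min/day.

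If the top share p on a normal attendance propensity is compared with all controls:

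spurious difference = ρ × φ(z₁₋ₚ)/p × SD

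| Share reaching 80% | ρ = 0.1 | ρ = 0.2 | ρ = 0.3 |
|---|---|---|---|
| 50% | 1.15 | 2.29 | 3.44 |
| 60% | 0.93 | 1.85 | 2.78 |
| 70% | 0.71 | 1.43 | 2.14 |
| 80% | 0.50 | 1.01 | 1.51 |
| 90% | 0.28 | 0.56 | 0.84 |

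(min/day, SD 14.4)

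The range is 0.28 to 3.44 min/day, which is 6% (0.28/5) to 69% (3.44/5) of the target. With the unadjusted SD of 17.8 it would be 0.35 to 4.26 min/day. The adjusted figures suit this plan better, because it analyses change from baseline with a repeated-measures analysis of covariance.

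**The case against.** The case on the other side has five parts.

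- **Low stakes.** This is one supportive analysis beside an intention-to-treat model, multiple imputation and complete-case analysis. No decision rests on it. This stands. A reader might infer that the trial's main result is compromised, but the documents do not support that, because the primary analysis keeps everyone as randomised.

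- **Silence about controls.** An article condenses a fuller plan, which might set a control rule such as attendance at usual physical education. This stands in part. A reader might also infer that the rule, taken literally, deletes the whole control arm. A between-group analysis cannot be meant to have no controls, so that reading should not be pressed. What remains is that the article fixes an attendance criterion that exists in one arm and states no rule for the other.

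- **Common to all per-protocol analyses.** Loss of randomisation is generic and contradicts nothing by itself. True, but here the analysis carries a purpose it cannot serve, and it sits under a statement that all analyses follow intention-to-treat. Those faults are in this text.

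- **Assumed size.** Neither the attendance share nor the correlation is documented. Sessions run inside scheduled lessons, so attendance may largely reflect being at school. At 80-90% attending and ρ = 0.1, the difference is only 0.28 to 0.50 min/day. This stands, which is why a range is given. The documents do not show that the bias will be large, or that the result would be presented as proof of efficacy.

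- **The obvious replacement has its own flaw.** A complier-average effect at a binary 80% cut assumes that allocation acts only through reaching 80%. Pedometer goals, WhatsApp messages to students and parents, and partial attendance can all act below that cut. If 60% complied and everyone gained 5 min/day, the estimate would be 5/0.6 = 8.3 min/day. This stands and shapes the fix. Even so, an estimate that uses allocation as instrument centres on zero when allocation has no effect, and the attender comparison does not.

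**Conclusion.** The point holds as a correction to a supportive analysis. The mismatch between the missingness purpose and the attendance rule is plain on the face of the text and needs no assumption. So is the departure from the intention-to-treat statement in the same section. That the comparison is selected attenders against unselected controls follows from sessions being offered in one arm only and from the absence of a control rule.

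The size is conditional. Over the assumed grid it is about 0.3 to 3.4 min/day against a target of 5. The upper end needs both a low share of attenders and the highest correlation considered. The upward direction assumes that attenders are the more active students, which is plausible but not documented. If attendance is linked to MVPA mainly through baseline activity, adjustment removes much of the bias and the lower values apply.

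**What to change.** Amend the Analysis plan as follows.

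1. Remove the missingness purpose from this analysis. Leave that question to the multiple imputation and complete-case analyses already listed.
2. Call it a non-randomised adherence analysis, exempt it explicitly from the intention-to-treat statement, and say that it is not evidence of efficacy.
3. State that control students are kept unselected.
4. If an adherence-adjusted effect is wanted, estimate it with randomised arm as instrument for the number of sessions attended, using the same covariates and cluster structure as the main model. State beside it that the exclusion restriction is doubtful: pedometer goals and messages act independently of attendance, so the estimate may overstate the effect of the sessions. Using a count of sessions eases the threshold problem but not this one.
5. Reconcile the 16-week and 24-week programme lengths across the Abstract, Study objectives, Intervention, Table 1 and Discussion, and then give the number of sessions that the 80% refers to.

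The cost is small. Items 1 to 3 and 5 are wording. Item 4 is one extra model on attendance data already collected for the process evaluation, and its interval will be wider than that of the direct comparison.

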
**Fig 2 pone.0272629.g002:**
[figure not shown]
Hypothesized mediators of physical activity behavior change.

### Data management

All data will be entered into the database using unique study codes for each participant and will be securely stored on a password-protected computer. The data manager, who is independent of competing interests, can only access the data. A Data Monitoring Committee is not needed since the study is minimal risk. Important protocol modifications during this study will be regularly communicated and updated on the Clinical Trial Registry and the journal of publication. No later than three years after collecting the 48-Weeks end-line assessment from baseline, we will deliver a wholly without identified data set to an appropriate data archive for sharing purposes.

### Patient and public involvement

The study will be conducted in secondary public schools in Jacarezinho and participants (i.e., students and teachers) will be invited to provide feedback on the intervention and suggestions for further improvement, which will be used to refine the ActTeens Program intervention components and implementation strategies. The findings of this trial will be published in peer-reviewed journals, irrespective of the direction or magnitude of the results, and will also be presented both to the Regional Education Center of Jacarezinho and participating schools through a report outlining the findings.

## Discussion

It is widely acknowledged that the health benefits of participation in PA are not limited to physical health but also incorporate metabolic and mental components [2]. Despite the importance of PA, data from the Brazilian Scholar Health Survey (PeNSE in Portuguese) found that the prevalence of Brazilian adolescents who met the PA guidelines was extremely low [5]. The *ActTeens* trial will investigate the impact of a 16-weeks of PA program on physical activity levels, fitness, cardiometabolic and mental health in adolescents. The findings of this trial will contribute to the growing evidence around PA interventions in low-and- middle-income countries, which are still scarce, particularly in South America.

The *ActTeens Program* (adaptation of the Australian RT for Teens program) [34] aims to provide students with additional PA opportunities within the school day, to increase fitness and physical activity levels. It also includes self-monitoring, individualized goal-setting, and parent involvement to promote active behavior out-of-school. Strategies included within ActTeens will be guided by self-determination theory and social cognitive theory, which will endeavor to satisfy students’ basic psychological needs (autonomy, competence, and relatedness) and promote self-efficacy, respectively. The hypothesis is that the intervention will effectively be improving fitness levels, cardiometabolic and mental health, and increase the physical activity levels of adolescents.

The structured PA sessions will be specifically designed to provide adolescents with the knowledge, skills, and new opportunities to engage in PA through resistance training focusing on enhancing muscular fitness. Evidence that additional resistance training during PE classes has a positive impact on screen-time [37, 38], body composition [73], muscular fitness [34, 37, 73], resistance training skill competence [34, 37], self-efficacy [34], autonomous motivation for PA [34], and well-being [36]. The structured sessions of ActTeens Program could offer a feasible method to improve CRF and muscular fitness within PE classes. Further potential advantages are its scalability and ease of dissemination [47, 74] since this intervention may be incorporated into PE lessons without taking up additional PE time; it should not interfere with the normal curriculum and does not require extensive training of teachers.

To address students’ PA levels throughout the entire day and promote PA outside of school, the program will include behavior change strategies such as self-monitoring and individualized goal-setting through pedometer use, and parent involvement (social support). The pedometer will be strategies that might have a large potential to motivate the PA practice daily, since adolescents have the freedom to choose when, how, and with whom he/she wants to be physically active to reach/ increase the steps/day [32]. The parents will play as encouragers for their children to be physically active in the home environment since social support is a determining and have a pivotal role in behavioral change and adherence to a healthy lifestyle.

The strengths of the ActTeens Program include: 1) a new PA opportunity different from the traditional activities that have been focused for PE lessons; 2) individualized goal-setting of steps/days; 3) autonomy of adolescents to choose which exercise/activities to do both during structures sessions and out-of-school to achieve the goal. Furthermore, all participants will be followed up for 12 months after the intervention period. A long follow-up period is clinically relevant but has not been previously investigated in Brazilian adolescents. Extended follow-up will provide information on maintenance of health effects and long-term outcomes (eg, effects on metabolic markers).

In conclusion, the current study will provide evidence regarding the impact of a PA intervention on fitness, active lifestyle, cardiometabolic and mental health over the short and long-term in adolescents, with potential to debates about design and implement of PA interventions in low-and- middle-income countries.
